| Sample Size:      | 15 women and their infants (participants who do not complete treatment or report less than 85% adherence will be replaced)                                                                                                                                                                                                                                                              |
| Study Population: | Pregnant women diagnosed with genotype 1, 4, 5, or 6 chronic hepatitis C infection that are between the ages of 18 and 39 and are 14 + 0 and 22 + 6 weeks of gestation at Screening                                                                                                                                                                                                     |
| Study Site:       | Magee-Womens Hospital of UPMC, Pittsburgh, PA                                                                                                                                                                                                                                                                                                                                           |
| Study Design:     | Single-site, single-arm pilot study                                                                                                                                                                                                                                                                                                                                                     |
| Study Duration:   | Approximately 28 weeks per maternal participant and one year of infant follow up.                                                                                                                                                                                                                                                                                                       |
| Study Medication: | Fixed-dose combination tablet of Ledipasvir 90 mg and Sofosbuvir 400 mg (LDV/SOF FDC)                                                                                                                                                                                                                                                                                                   |

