| ION-2 | LDV/SOF (12)       | PEG-INF + RBV | 109 | 102 | 7  | 94 (87-97)  |
|       | LDV/SOF + RBV (12) | PEG-INF + RBV | 111 | 107 | 4  | 96 (91-99)  |
|       | LDV/SOF (24)       | PEG-INF + RBV | 109 | 108 | 0  | 99 (95-100) |
|       | LDV/SOF + RBV (24) | PEG-INF + RBV | 111 | 110 | 1  | 99 (95-100) |
| ION-3 | LDV/SOF (8)        | No            | 215 | 202 | 11 | 94 (90-97)  |
|       | LDV/SOF + RBV (8)  | No            | 216 | 201 | 9  | 93 (89-96)  |
|       | LDV/SOF (12)       | No            | 216 | 206 | 3  | 95 (92-98)  |

Clinical studies of HCV genotype 4 treatment with LDV/SOF include two open-label studies of 43 participants. The SYNERGY trial evaluated 12 weeks of LDV/SOF in 21 patients, of whom 60% were treatment-naïve and 43% had advanced fibrosis. One participant withdrew consent, but the rest achieved SVR12 (20/21). The other study enrolled 22 treatment naïve genotype 4 patients, 21 achieved SVR12 with a 12 week course of LDV/SOF. Similarly, an open-label study of 41 patient with HCV genotype 5 infection were treated with a 12 week course of LDV/SOF and 95% achieved SVR12. A small, two-center, open-label study investigated efficacy of ledipasvir/sofosbuvir for 12 weeks in treatment-naïve and -experienced patients with HCV genotype 6 infection with 24 of 25 patients achieving SVR12 (96%).

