#### **5.1.2 Retention**

The importance of retention will be stressed to the participant at each visit as part of protocol adherence counseling. Once a participant is enrolled, the study staff will make every effort to retain the participants in follow-up to minimize possible bias associated with loss-to-follow-up. Any participant that discontinues the study before the PK3 visit is completed or if a participant reports missing more than 1 dose per week averaged over the duration of the study then they will be replaced by recruiting another participant into the study. We anticipate needing to replace no more than two participants.

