#### 7.4.4 Post Treatment (V7) Visit

The following procedures will occur at the Post Treatment visit (V7), which should be scheduled 12 weeks  $\pm$  4 days from the last dose of study medication. The V7 visit can occur simultaneously with the 8 week Follow-up Visit for the infant (iV1). This is the last scheduled clinic visit for the maternal participant.

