## 7.5 Follow-up Procedures for Participants Who Permanently Discontinue Study Medication

Participants will be permanently discontinued for significant laboratory abnormalities or adverse events as outlined in section 9.3 and 9.4, if they miss greater one dose per week (averaged over the duration of the study), or if they choose to discontinue the study medication. Participants who are permanently discontinued from the study will be instructed to return the study medication and study medication log. All protocol-specified study procedures will continue for safety except the following:

- Provision of study medication
- Provision of medication use adherence counseling

The following procedures will be performed at the visit in which study medication use is permanently discontinued:

- Collection of blood for PK analysis (single time point)
- HCV resistance testing
- Viral load as needed (i.e. participant withdraws, investigator opinion)
- Medical history review
- Concomitant medication review
- Brief physical examination including vital signs, if indicated.

The participant will be asked to continue in the study and complete all remaining scheduled maternal and infant visits per protocol for safety.

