### **9.3 General Criteria for Permanent Discontinuation of Study Medication**

A participant will be permanently discontinued from medication use by the physician investigators for any of the following reasons, according to the HCV treatment guidelines:

- 5-fold or greater increase in ALT or AST at the PK1 or PK2 visit compared to baseline result (Screening visit), confirmed by immediate repeat testing
- Any increase of ALT or AST of less than 5-fold from baseline (Screening visit) at the PK1 or PK2 visit that is accompanied by any weakness, nausea, vomiting, or jaundice
- 3-fold or greater increase in ALT or AST accompanied by bilirubin >2x the upper limit of normal, confirmed on immediate repeat testing
- Increase HCV RNA viral load by greater than 10-fold at PK2 visit (6-8 weeks after starting treatment)
- Participant is unable or unwilling to comply with required study procedures
- If the participant delivers prematurely (and is still on study medication) and desires to breastfeed
- Participant might be put at undue risk to their safety and well-being by continuing medication use, according to the judgment of the study investigators. The study investigators will consult with the independent safety physician prior to all study medication discontinuation instituted for this reason.

Any time a participant is permanently discontinued from study medication (prior to completion of the 12 week course of study medication), HCV resistance testing will be performed.

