### **10.5.2 Analysis of SVR12**

Outside of pregnancy, 96% of patients treated with LDV/SOF for 12 weeks obtained an SVR12. In this pilot study, we estimate that at least 14 out of the 15 chronically HCV-infected pregnant women will have a SVR12 after treatment. Participants who do not complete the treatment course or report low adherence will be excluded from the analysis.

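### The only planned SVR12 rate (10.5.2) excludes non-completers and low adherers, so it can omit women stopped for virologic failure and has a different denominator from the 96% quoted beside it

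*Protocol*

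**What the plan says.** Section 10.5.2 opens with a benchmark: "Outside of pregnancy, 96% of patients treated with LDV/SOF for 12 weeks obtained an SVR12". It then expects SVR12 in at least 14 of 15 women and ends with the exclusion: "Participants who do not complete the treatment course or report low adherence will be excluded from the analysis". It makes no exception for the reason treatment stopped, and the protocol states no other SVR12 analysis set.

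Three other parts of the protocol bear on this rule.

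- **Stopping.** Section 9.3 lists among its reasons for permanent discontinuation "Increase HCV RNA viral load by greater than 10-fold at PK2 visit", which it places 6-8 weeks after the start of treatment. Section 9.4 also ends treatment for Grade 3 or 4 adverse events judged related.
- **Replacement.** The synopsis says that "participants who do not complete treatment or report less than 85% adherence will be replaced". Section 5.1.2 adds: "We anticipate needing to replace no more than two participants".
- **Follow-up after stopping.** Section 7.5 says: "The participant will be asked to continue in the study and complete all remaining scheduled maternal and infant visits per protocol for safety". Section 7.4.4 sets V7 at 12 weeks plus or minus "4 days from the last dose of study medication", and the V7 table includes HCV RNA.

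**The concern.** A more than 10-fold viral rise on treatment is the clearest sign that the regimen is failing. Under 9.3 the woman must stop, so she cannot complete the course, and 10.5.2 then drops her because she did not complete it. Removing a known failure from the denominator can only raise the rate. Removing women who stopped for other reasons, or who reported low adherence, raises it if they are cured less often than completers.

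This touches the study's own question. Section 2.5 notes higher HCV RNA in pregnancy, and section 13.3.1 warns that the dose may be inadequate for pregnant women and that resistance could follow. SVR12 is the one maternal virologic outcome among the endpoints in 10.2.2. A completer rate near 93% could be read as close to the non-pregnant 96% although the two figures count different people.

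**Working it through.** **1. The protocol's own figures.** Table 2 (section 2.4.1) gives, for the 12-week LDV/SOF arms without ribavirin:

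| Trial | N | SVR12 | Listed treatment failures | Other without SVR12 |
|---|---|---|---|---|
| ION-1 | 214 | 211 | 1 | 2 |
| ION-2 | 109 | 102 | 7 | 0 |
| ION-3 | 216 | 206 | 3 | 7 |
| Total | 539 | 519 | 11 | 9 |

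The pooled rate is 519/539 = 96.3%, which reproduces the 96%. The expected count also follows: 15 × 0.96 = 14.4, consistent with at least 14 of 15.

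**2. Whom the benchmark counts.** Of the 539 − 519 = 20 patients without SVR12, 11 are listed as treatment failures. The other 20 − 11 = 9 also stay in the denominator. Without those 9 the rate would be 519/530 = 97.9%. The genotype 4 trial described below Table 2 is handled the same way: 20 of 21, with the one withdrawal counted as not reaching SVR12.

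**3. Whom this trial would count.** A virologic stop occurs at weeks 6-8 of 12, so the woman is a non-completer. By 10.5.2 she is not analysed, and by the synopsis another woman takes her place. The analysed number returns to 15, and the failure does not appear in the rate.

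**4. Size, as an illustration.** Assume the protocol's expected 14 responders among 15 analysed women, and add k excluded women who have been replaced. The all-treated rate is (14 + c)/(15 + k), where c is the number of excluded women who reach SVR12. Intervals are exact (Clopper-Pearson) 95%.

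| Excluded and replaced (k) | Rate under 10.5.2 | All-treated rate |
|---|---|---|
| 0 | 14/15 = 93.3% (68.1-99.8) | 14/15 = 93.3% (68.1-99.8) |
| 1, virologic stop (c = 0) | 14/15 = 93.3% | 14/16 = 87.5% (61.7-98.4) |
| 2, neither cured (c = 0) | 14/15 = 93.3% | 14/17 = 82.4% (56.6-96.2) |
| 2, both cured (c = 2) | 14/15 = 93.3% | 16/17 = 94.1% (71.3-99.9) |

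Two is the largest number of replacements the protocol anticipates. The rate under 10.5.2 is the same in every row, whatever happened to the excluded women.

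**The case against.** The strongest defence is that no comparison is planned. Section 10.5.2 uses 96% to justify an expectation, whereas 10.5.3 does name a historical comparison and a chi-square test. This stands: a reader might infer that SVR12 will be tested against 96%, and the protocol does not say so. All the intervals above contain 96%, so at this sample size the choice of denominator would not change a formal conclusion.

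Second, the synopsis words the objective as viral response after completing 12 weeks of treatment, and SVR12 is a secondary endpoint of a pharmacokinetic pilot. That supports reporting a completer rate. It does not support making it the only rate, beside a figure for all patients treated.

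Third, the benchmark argument is partly inference. The 96% in 10.5.2 carries no citation, and section 2.1 gives it as approximate, with an exception for prior null responders with cirrhosis. Table 2 does not define treatment failure. A reader might infer that the 9 other patients were dropouts; the table does not say why they missed SVR12. What it does show is that they were counted.

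Fourth, a virologic stop would not vanish from the record. Early discontinuations are documented on case report forms and trigger resistance testing, and HCV RNA is also measured at several other visits. This is correct, but the woman would still be absent from the SVR12 rate.

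**Conclusion.** The point holds as a matter of definition. Followed exactly, 10.5.2 yields a rate conditional on completing treatment with adequate reported adherence. It can leave out clear virologic failures, and its denominator differs from that of the 96% beside it.

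Its size depends on how many women are excluded and on their outcomes, and the protocol gives no rate for either. With no exclusions there is no effect. With one replaced virologic stop the difference is 93.3 − 87.5 = 5.8 percentage points. With two replaced women it runs from 93.3 − 82.4 = 10.9 points too high to 94.1 − 93.3 = 0.8 points too low. All of this assumes 14 responders among 15 analysed women. A reader might infer that the planned rate is bound to be inflated; only the removal of known failures has a certain direction, because some women who stop for other reasons may still be cured.

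The change should be made: the bias is avoidable and the data are already due to be collected. The point does not call for any change to the stopping rules or to replacement for the pharmacokinetic objective.

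**What to change.** Replace the last sentence of 10.5.2 with:

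> SVR12 is analysed in all women who took at least one dose. Women stopped for virologic reasons or with no V7 HCV RNA result count as failures; other stopped or low-adherence women are counted by their V7 result. The rate is reported with an exact 95% CI. The rate among women who completed treatment with adequate adherence is supportive.

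The cost is protocol wording. Stopped women are already asked to attend their remaining visits, and V7 is timed from the last dose and includes HCV RNA, so no visit or sample is added. Replacement of participants for the pharmacokinetic objective is unchanged. The downside for the sponsor is that the SVR12 rate may be less favourable.

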### **10.5.3 Analysis of Safety Endpoints**

Rates of abnormal safety laboratory assessments will be compared to those reported in the literature on historic controls and rates of adverse pregnancy outcomes will be compared to historic HCV-infected pregnant women who have delivered at our institution. Statistical significance will be determined by chi-square test.

### **10.5.4 Data and Safety Monitoring Plan**

No Data and Safety Monitoring Board oversight is planned for this study, however a Study Steering Committee comprised by the Protocol Chair, a second physician investigator from the University of Pittsburgh, a laboratory scientist from the University of Pittsburgh, the Data Management lead statistician and a representative from Gilead Sciences Clinical Research will provide oversight. Reviews of study progress, including rates of participant accrual, retention, completion of primary and main secondary endpoint assessments will take place approximately every 3

months, and as needed. At the time of these reviews, or at any other time, the Study Steering Committee may recommend that the study proceed as designed, proceed with design modifications, or be discontinued. An independent safety physician experienced with monitoring of clinical trials among pregnant women will conduct interim safety reviews on a monthly basis or more frequently at the request of the Study Steering Committee.

## **11 DATA HANDLING AND RECORDKEEPING**

### **11.1 Data Management Responsibilities**

Study CRFs will be developed by the study team in conjunction with data management.

### **11.2 Source Documents and Access to Source Data/Documents**

The site will maintain source data/documents in accordance with current DAIDS policies. (<http://rsc.tech-res.com/policiesandregulations/>)

The study team will maintain, and store securely, complete, accurate and current study records throughout the study. In accordance with U.S. regulations regarding testing investigational medications, the study investigator will maintain all study documentation for at least two years following the date of marketing approval for the study medications being tested for the indication in which they were studied. If no marketing application is filed, or if the application is not approved, the records will be retained for two years after the investigation is discontinued and the US FDA is notified. For research involving children, records shall be retained at least until the pediatric subject reaches the age of 23.

Study records will be maintained on site for the entire period of study implementation.

### **11.3 Quality Control and Quality Assurance**

The study site will conduct quality control and quality assurance procedures in accordance with site SOPs.

## **12 CLINICAL SITE MONITORING**

As this is an investigator initiated IND study, monitoring will be performed by internal clinical study staff (i.e. QA/QC Reviewer), PoR, laboratory staff and local data management team. Internal reviews will include:

- Review informed consent forms, protocol procedures, and study documentation

- Assess compliance with the study protocol, Good Clinical Practices (GCP) guidelines, and applicable regulatory requirements (US and non-US), including CFR Title 45 Part 46 and Title 21 Parts 50, 56, and 312
- Perform source document verification to ensure the accuracy and completeness of study data
- Verify proper collection and storage of biological specimens
- Verify proper storage, dispensing, and accountability of investigational study medications

The Education and Compliance Office for Human Subject Research (ECO-HSR), Research Conduct and Compliance Office will also oversee study activities. The ECO-HSR has extensive experience in the auditing and monitoring of clinical investigations for compliance with GCP standards and IND commitments. To ensure appropriate institutional oversight of University-based IND applications, the ECO-HSR will periodically monitor the research oversight programs of IND Sponsors, which will include compliance of the Sponsor and Investigator with applicable FDA regulations, applicable University of Pittsburgh policies and the IRB-approved protocol and consent document. The frequency of these monitoring visits shall be determined by the ECO-HSR.

The study investigators also will allow inspection of all study-related documentation by authorized representatives of Gilead Sciences, FDA, OHRP, IRBs/ECs and other local and US regulatory authorities.

## **13 HUMAN SUBJECTS PROTECTIONS**

Study investigators will make efforts to minimize risks to participants. Informed consent will be reviewed in detail with potential participants and all questions will be adequately answered prior to obtaining written informed consent. All eligibility criteria will be verified prior to initiation of investigational product. Recruitment will begin after receiving IRB approval and after the protocol has been submitted to the FDA. The study investigators will permit audits by the NIH, Gilead Sciences, the FDA, OHRP, IRB, and other local and US regulatory authorities or any of their appointed agents.

### **13.1 Institutional Review Boards**

The study staff will ensure that the protocol, associated informed consent form, and study-related documents (such as participant education and recruitment materials) are reviewed and approved by the University of Pittsburgh IRB prior to starting the study. Any amendments to the protocol or informed consent will be approved by the University of Pittsburgh IRB prior to implementation.

## 13.2 Study Coordination

[name] MSc holds the Investigational New Drug (IND) application for this study. Assignment of all sponsor responsibilities for this study will be specified in a Clinical Trials Agreement (CTA) executed by the University of Pittsburgh and Gilead Sciences.

Close coordination between the study team is necessary to track recruitment, enrollment, retention, AEs and unanticipated problems and to address other issues that may arise in a timely manner. The study investigators and the independent safety physician will address issues related to study eligibility, AE management/reporting and unanticipated problems as needed to assure consistency. Rates of accrual, protocol adherence, retention, and AE incidence will be reported by data management and monitored closely by the team as well as the Study Steering Committee.

## 13.3 Risk Benefit Statement

### 13.3.1 Risks

#### General/Maternal

As with any research study, there may be adverse events or side effects for the maternal participant or the fetus/infant that are currently unknown and certain of these unknown risks could be permanent, severe or life-threatening.

There are no studies of LDV/SOF in pregnant women. There have been animal studies done in rats and rabbits as detailed in section 2.4.2. No effects on fetal development have been observed in rats and rabbits at the highest doses tested. However, animal reproductive studies are not always predictive of human response.

It is also not known if LDV/SOF is present in human breast milk. If the participant delivers while still on study medication and intends to breast feed, study medication will be discontinued and HCV resistance testing will be done at the next study visit.

There is a potential risk that the hepatitis virus may become resistant to LDV/SOF because the dose may not be adequate for treating pregnant women with hepatitis C or if the participant does not complete the entire 12 weeks of study medication. If resistance occurs, this may limit the choices of effective therapy after pregnancy for the participant and/or possibly her infant.

The following side effects have been associated with the use of oral LDV/SOF used daily for 12 weeks of duration in men and non-pregnant women:

|         | Percentage of Participants
N=539 |
|---------|-------------------------------------|
| Fatigue | 13%                                 |

|          |     |
|----------|-----|
| Headache | 14% |
| Nausea   | 7%  |
| Diarrhea | 3%  |
| Insomnia | 5%  |

There are risks of alterations in laboratory values with the use of this medication. Previous studies have shown the following:

Bilirubin Elevations: Bilirubin elevations of greater than 1.5x the upper limit of normal were observed in <1% of subjects treated with LDV/SOF for 12 weeks.

Lipase Elevations: Transient, asymptomatic lipase elevations of greater than 3x the upper limit of normal were observed in 2% of subjects treated with LDV/SOF 12 weeks.

Creatine Kinase: Creatine kinase was not assessed in Phase 3 trials of LDV/SOF FDC. Isolated, asymptomatic creatine kinase elevations (Grade 3 or 4) have been previously reported in subjects treated with sofosbuvir in combination with ribavirin or peginterferon/ribavirin in other clinical trials.

There are known drug interactions with LDV/SOF and other prescription and non-prescription medications. A comprehensive list of medications will be obtained from participants including over-the-counter medications (i.e. antacids, St. John's wort) and compared to the package insert to assess any contraindication to participation or necessary alterations in dosing schedules with use of the study medication.

There is a risk of Hepatitis B virus (HBV) reactivation while receiving treatment for HCV in patients who are co-infected with HBV and HCV. HBV reactivation has been reported, in some cases resulting in fulminant hepatitis, hepatic failure and death.

Phlebotomy or starting an IV may lead to excessive bleeding, discomfort, feelings of dizziness or faintness, and/or bruising, swelling and/or infection.

Disclosure of HIV status may cause worry, sadness or depression. Disclosure of HIV-positive status has been associated with depression, suicidal ideation, and denial as well as social isolation. Trained counselors will be available to help participants deal with these feelings.

Participation in clinical research includes the risks of confidentiality loss.

Participants will be asked to provide personal/protected health information (PHI). All attempts will be made to keep PHI confidential within the limits of the law. However, there is a chance that unauthorized persons will see PHI. All paper records will be kept in a locked file cabinet or maintained in a locked room at Magee. Electronic files will be password protected. Only people who are involved in the conduct, oversight, monitoring, or auditing of this study will be allowed access to the PHI that is collected. Any publications from this study will not use information that will identify participants

by name. Organizations that may inspect and/or copy research records maintained at the participating sites for quality assurance and data analysis include groups such as the study sponsor, the National Institute of Health (NIH) or its designee and the US Food and Drug Administration (FDA).

